## 4. Conclusions

This study is aimed at manualizing and systematizing the application of the MBSR-P intervention, as well as rigorously studying both its processes and its effects, with the purpose of being able to generalize its use and provide knowledge about its effectiveness, contributing to the design of a new parental support proposal for groups with specific needs, such as parents of children and adolescents with mental disorders.

The careful study of the program will provide a breakthrough in its understanding via analysis of the aspects involved in the processes of change through the experience of the participants in the meditation practices, which will help not only to provide evidence, but also to identify the key components of the interventions based on mindfulness and its implication in the changes.

Likewise, the analysis of the application of meditation practices to daily life can help to identify the challenges to achieving its transferability. These challenges and limitations may be related to both the participants and the components of the program, as well as its implementation. Addressing these limitations will give us clues about the keys to guaranteeing transferability, which has important implications at both the research and intervention levels.

## Figures and Tables

**Figure 1 ijerph-18-10777-f001:**
[figure not shown]
Evaluation process of the MBSR-P intervention program.

**Figure 2 ijerph-18-10777-f002:**
[figure not shown]
Steps for quantitative data analysis.

**Figure 3 ijerph-18-10777-f003:**
[figure not shown]
Steps for qualitative data analysis.

**Table 1 ijerph-18-10777-t001:** Sessions and contents of the MBSR-P.

Session	Contents
1	Informative session: Presentations, brief explanation of the program, guidelines to follow during the program, group norms, and recommendations to obtain the maximum benefit. Pre-test sociodemographic and effectiveness instruments battery;
2	Introduction to mindfulness: Theoretical and conceptual bases of the program, application of self-regulation skills, and introductory breathing practices. Theoretical explanation of the seven bases of mindfulness, such as nonjudgement, trusting, and beginner’s mind. Some of the practices will include the raising exercise to refine the senses and be aware of how one perceives one’s experiences through one’s senses. Home practices will be 10 min meditations focusing on breathing;
3	Finding your anchor: Meditation centered on breathing, and the foundation of the mindfulness triangle of thoughts, emotions, and sensations. Introduction of some inspirational readings, so as to be aware of the emotions, thoughts and sensations that emerge during those readings. Home practices will be 2 min breathing exercises and inspirational readings to observe the triangle previously described;
4	Corporal scanning: Conscious stretching exercises. Body scan, guiding practice so as to be able to become aware of the sensations that are emerging through attention to breathing. Sequenced aware movements will also be introduced. Home practices will be 10 min meditations and a calendar of positive events, where participants will write down certain positive events that have happened throughout the week in a systematic way, following certain directions;
5	Connecting with stress: Reflection on stressful experiences, how they are coped with, and how they interfere with daily life (being aware of their emotional reactivity and behavioral patterns). Identification and naming of the stressors in their parenting role. Distinction between reacting and responding to stress, being aware of their reactivity in those stressful situations and learning to put a stop to it; One-to-one communication dynamic to help the participants to be aware of their own active hearing and their communication patterns, and how a lot of their parenting stressors are related to communication problems. Group sharing of the calendar of positive events and their parenting experience, also connecting their own parenting experiences and the pain and difficulties they have faced with their physical experience. Home practices will be 24 min meditations and a calendar of negative events;
6	Open meditation: Meditation with the five elements: breathing, body, sounds, thoughts as conscious events (differentiating the event from the content), and open presence (receive what there is in the present moment). Group sharing of the calendar of negative events. Incorporation of more silent spaces in the guided meditations. Second communicative dynamic, with a focus on coping strategies focused on the problem and the emotion. The session will finish with an inspirational reading. Home practices will be 24 min meditations, and applying the reactivity versus responding in those situations that are stressors for them. Conscious movements and watching of audiovisual material with a focus on parenting (being aware that parenting involves letting go and giving life for them to be autonomous). Questionnaire to evaluate the feedback of the intervention process;
7	Relating to new experiences: Group dynamic that makes the participants change their sitting place and change their routine, reflecting on how that change influences their thoughts, emotions, and bodily experiences. Transformational coping strategies, attitudes, and behaviors that improve psychological characteristics such as strength in the face of stress or resilience. Group dynamic on relational styles (role-playing with the different relational styles and after group discussion). Emphasis on the internal resources and being able to identify them. Communication dynamic to identify different communication patterns, with participants identifying their own communication styles. Learning of other anchors besides breathing. Questionnaire to evaluate the feedback of the intervention process. Home practices will be 24 min meditations;
8	Strengthening learning (intensive day): Day of silence, application of MBSR-based skills in different life situations. Emphasis on the awareness of the present moment and silent sharing with other parents. Importance of walking meditation. Emphasis on the fact that this day does not necessarily involve a nice experience, and acceptance of this uncomfortable experience;
9	Listen to yourself: Meditation practices in silence without guidance. Discovering inner voices through guided meditations and encouraging personal reflection. Reflection on what the participants want to remember, what they have learned about themselves, and things that they have been emotional about. Writing of a letter with three short-term challenges and long-term challenges, and the possible barriers. Introduction of the positive parenting sessions;
10	Specific positive parenting session: Emphasis on the complexity of the parenting role and reflection on how each person’s own history shapes how they are as parents, working on the awareness of their established patterns as a parent. Attachment and communication along with the promotion of autonomy in their children. Communication dynamics based on listening with full attention, non-judgmental acceptance, and compassion. Additionally, assertive communication strategies, with an emphasis on being aware of the child’s thoughts and feelings and not judging them while talking to them;
11	Specific positive parenting session: Parenting practices related to establishing limits without being authoritarian, adapting those practices to the developmental period of their children and the importance of negotiation, particularly during adolescence. Focus on self-regulation and expectations as key elements to avoid the escalation of possible conflictive situations. Role-playing of emerging situations related to their parenting roles. For example, a common emergent situation would be a child arriving home after curfew. Parents represent those situations and work on how to avoid reacting rather than responding, how to handle their emotions, and how to be aware of their own and their child’s responses. Post-test effectiveness and satisfaction instruments battery and discussion group.

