#### 2.2.3. Perceived Impact by the Participants and Implementation Analysis of the Program

In order to evaluate the perceived impact by the participants and the implementation of the program, halfway through the intervention, in the sixth session, the participants will fill out a questionnaire composed of nine open questions designed ad hoc to obtain feedback from the participants on the intervention process (Table A2). The questions will refer to the expectations met up to that moment, the learning obtained and its integration into daily life, the changes perceived, the implementation of the practices, the difficulties encountered, and the methodology used (e.g., “Do you notice changes in the physical body/mind as a result of these practices?”). These questions were based on the mid-program questions proposed in the original MBSR; the authors then adapted them to the program and intervention context, incorporating questions considered relevant by the authors—who have experience in program evaluation—to adequately fit the characteristics of this intervention. The open questions were developed so that they were relevant, clear, concise, and specific, without overlapping with others. Finally, a practitioner with experience in mindfulness interventions reviewed the questions and adapted their language and formulation [59].

Moreover, the professional who leads the group will fill out a field diary after each intervention session, where information will be collected about the implementation of the program, as well as the group dynamics and the implementation of informal practices at home (Table A3). The questions will have both open and closed answers (e.g., “Any notable issues in the session? Strengths of the program, aspects of the program that have not worked well, or other observations about the course of the session”).

A discussion group will be carried out at post-test (in the last session), in which the following questions will be presented: (a) “Are you satisfied with the program? What has it given you in a personal and professional context?”; (b) “What are the elements or components of the program that have helped you the most? Why?”; (c) “What do you think about the intervention being carried out in a group? Has it helped/contributed or not? In what way?”; (d) “What moments in the intervention would you consider to be the turning point for you?”; and (e) “What do you think could be improved about the program in the future?”.

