#### 2.5.2. Process Evaluation

In the first meeting, the participants will be informed about how the program will be carried out, the general objectives of the program, their participation in it, the content of the sessions, the importance of their engagement with all of the sessions, the materials that will be needed, and the guidelines to follow throughout the process, such as carrying out activities at home. Once the information has been received and any doubts clarified, if they agree with all of the points, the participants will sign an informed consent form in accordance with the Declaration of Helsinki [65], in which they will be informed that the discussion group will be audio recorded, and that confidentiality will be ensured for all participants. The informed consent will also notify the participants that they can leave the intervention at any time without this decision having any consequences. There will be no financial or other incentives for participation.

In this first session, the pre-test data from the battery of self-administered questionnaires will be collected (including both the sociodemographic profiles and the effectiveness measures) from the intervention group. In the intermediate phase of the intervention (sixth session), the participants will fill out the questionnaire to evaluate the feedback of the intervention process up until that moment. At the end of the intervention, the post-test data from the battery of effectiveness and satisfaction self-administered questionnaires will be collected, and the discussion group will be held. Furthermore, during the intervention process, after each session, the professional in charge of the implementation will fill out the field diary corresponding to each session once the session is over. Over a period of 6 months after the end of the intervention, the follow-up will be carried out, in which the battery of instruments referring to the effectiveness of the intervention will be administered to the participants, in addition to the follow-up questionnaire aimed at evaluating the application to daily life of the learning achieved through participation in the intervention.

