#### 2.6.2. Qualitative Data

For the management and coding of qualitative data, the qualitative analysis software NVIVO (QRS, Burlington, MA, USA) will be used [76]. With the information that the narratives of the participants will reveal, through the qualitative methodology, two types of analyses will be carried out depending on the information collected. On the one hand, an enumerative content analysis will be performed on the questionnaire of the intermediate phase of the intervention and on the follow-up questionnaire (Grbich, 2013, cit. in [77]). On the other hand, an inductive thematic analysis will be carried out without predetermined theoretical assumptions of the qualitative data from verbatim transcripts of the audio recordings from the discussion group [78]. The intermediate questionnaires will support the implementation analysis, and will feed the systematization of the intervention. The discussion groups will support the analysis of the mechanisms of change. Finally, the follow-up questionnaires will be useful for the examination of the transferability of the acquired practices to daily life.

The analyses will be conducted in parallel by two researchers with experience in qualitative methodology, along with an external supervisor. First, a code book will be built for each instrument following the recommendations of Braun and Clarke [78]: (1) to familiarize the researchers with the data, and (2) to generate initial codes. Additionally, for the thematic analysis, the recommendations of Braun and Clarke [78] corresponding to the study of the topics will be followed: (3) to search for themes; (4) to review the themes; (5) to define and name the themes; and (6) to write up the results.

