Once the category systems are created, the researchers will code separately and, subsequently, meet to discuss the categories and ascertain the degree of inter-observer reliability, which will be calculated by dividing the total number of agreements in the coding of all categories by the total number of agreements and disagreements in all categories [79]. Moreover, for the enumerative content analysis, the percentages of participants that have mentioned each category in their narrative will be calculated in order to obtain comparative data on which elements of the intervention are more frequently mentioned, and the areas in which the program has a greater impact on their daily lives. For the representation of these data, comparative graphs of the percentages of participants in each category will be made, and word clouds of the most common narratives in the categories will be provided. The word clouds will be created to identify the most frequent concepts that are talked about in the focus groups, organized by the previously identified categories and in a visual manner. To do so, a selection of the 50 most frequent words will be carried out, using as an inclusion criterion the length of the word (more than 3 letters). Secondly, words with the same root (e.g., parent and parenting) will be grouped under the same concept (e.g., “parenting”). Finally, we will eliminate linking and non-content words such as “between” or “element”. For the inductive thematic analysis, the two researchers will go back and forth through the data separately so as to identify possible themes. Later on, the proposed themes will be shared, and the researchers will discuss and not only agree on a set of themes, but also identify higher order themes and subthemes, define them in depth, and select quotes that represent those themes and subthemes.

To reach an adequate sample size that will enable us to carry out this content and thematic analysis using a representative sample, we will use the data saturation criteria. Taking into consideration the parameters proposed by Hennink et al. to estimate the sample size in focus groups, we will carry out between five and six focus groups so as to achieve both code and meaning saturation [80]. Code saturation is defined as the moment when no additional codes appear in the data, and meaning saturation is defined in terms of whether the qualitative data provide further information or insight on the codes [80].

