### 3.1. Expected Results

The MBSR-P program is a psychoeducational and multimodal intervention adapted from Jon-Kabat Zinn’s original MBSR [13,18], created for caregivers of children and adolescents with mental disorders. Although there is some evidence of effectiveness of the original MBSR program, this proposal seeks to optimally adjust the intervention program to the characteristics and circumstances of caregivers of children and adolescents with mental disorders. For this purpose, positive parenting contents will be incorporated throughout the intervention, two specific positive parenting sessions will be added, and the timing of the sessions and home practices will be modified. Thus, we expect the systematization of the intervention to guarantee the tailoring of the program to the specific needs and demands of this population [81]. The adaptation of the timing of the sessions and home practices take into consideration the already busy schedules of parents of children and adolescents with mental health problems [3,4]. The integration of the intervention in the mental health services considers their use of different services. We also expect to satisfy the demands of parents for both self-nourishing/self-care time and an improvement of parental competencies by incorporating positive parenting contents in a personal development psychoeducational intervention [3,4]. Moreover, with the systematization of the intervention, we also expect to maintain a high level of fidelity in the implementation of the intervention which, in turn, would guarantee the quality of the intervention, facilitating the acquisition of the intended objectives as well as their transferability to the participants’ daily lives [82].

The mixed-methods approach used in this study will help to provide different perspectives and complementary data of a different nature in order to obtain more complete information and understanding of how the program has an impact on different areas of parents’ lives, and how the learning obtained in the intervention context is integrated in the personal and family environment. It will also enable the more in-depth analysis of the implementation process and mechanisms of change, identifying strengths and weaknesses of the program [44].

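### As scheduled, the intervention group's post-test, satisfaction score and discussion-group themes would come only from parents still attending at session 11

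*Protocol article*

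**What the plan says.** For the intervention group, three collections share one place and time. Table 1 ends session 11, the last session, with "Post-test effectiveness and satisfaction instruments battery and discussion group". Section 2.2.3 agrees on the qualitative part: "A discussion group will be carried out at post-test (in the last session". Section 2.5.2 gives the timing in general terms: "At the end of the intervention, the post-test data from the battery of effectiveness and satisfaction self-administered questionnaires will be collected", with the discussion group held at the same point. Section 2.6.2 then assigns the qualitative roles, and "The discussion groups will support the analysis of the mechanisms of change".

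Mid-programme feedback is also an in-session form: "In the intermediate phase of the intervention (sixth session), the participants will fill out the questionnaire to evaluate the feedback". Table 1 lists it in session 6 and again in session 7.

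Section 2.5.2 states that the consent form tells parents "they can leave the intervention at any time without this decision having any consequences". Section 2.6.1 discards cases with data missing at questionnaire level. Controls come from the waiting list (section 2.4.2) and, under section 2.5.2, complete both batteries on the same terms and at matching times. The 6-month follow-up repeats the effectiveness battery and adds the Table A4 questionnaire. It is not tied to a session, and parents who left are not mentioned.

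**The concern.** Leaving a programme is not the same as leaving a study. Here the schedule makes the one lead to the other. A parent who stops partway, or is simply absent from session 11, gives no post-test, no satisfaction score (CSQ) and no discussion-group contribution unless someone seeks them out, and the article does not say that anyone will. The discard rule then removes that parent from the pre/post analysis.

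The loss falls on the questions the study most wants answered. The plan speaks of "identifying strengths and weaknesses of the program", and its discussion-group questions ask whether the group format helped or not. Parents for whom the programme did not work are plausibly over-represented among those absent at the end. The loss can also differ between arms, because an intervention parent must still be attending after about 3 months and 11 sessions, whereas a waiting-list parent has nothing to drop out of. The groups are not randomised, so this would add to whatever imbalance matching leaves. The limitations in section 3.2 do not mention it.

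**Working it through.** **1. What a parent contributes, by attendance, if the text is followed literally**

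- Stays to session 11: feedback form, post-test, CSQ, discussion group, 6-month measures.
- Leaves after session 6: feedback form, and possibly the 6-month measures; no post-test, CSQ or discussion group.
- Leaves before session 6: possibly the 6-month measures only.
- Control: pre-test and post-test, neither tied to programme attendance.

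The results that depend on session 11 are therefore the pre/post comparison, the CSQ mean and the discussion-group themes. The category percentages do not depend on it, because section 2.6.2 bases the enumerative content analysis on the mid-programme and follow-up questionnaires.

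**2. The plan's own sample-size figures (section 2.5.3)**

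Inputs: f = 0.25, α = 0.05, correlation ρ = 0.50, sphericity 1, power 0.80. With N participants and m measures, λ = f²·N·m/(1 − ρ).

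- Two groups, two measures: at N = 34, λ = 0.0625 × 34 × 2/0.5 = 8.5 with 1 and 32 df, power 0.807. N = 33 gives 0.795. The stated 34 is reproduced, as a total over both groups.
- One group, three measures: at N = 28, λ = 0.0625 × 28 × 3/0.5 = 10.5 with 2 and 54 df, power 0.812. N = 27 gives 0.796. The stated 28 is reproduced.

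**3. Is loss of power the problem?**

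The drop-out share d is not in the article, so 10%, 20% and 30% are assumptions. Of 34 intervention parents, 30, 27 or 23 would remain (rounded down). For the pre/post comparison, f = 0.25 with ρ = 0.50 corresponds to a between-group difference of 1 SD in change.

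| Intervention parents assessed | Pre/post power with 20 controls | Three-measure power, intervention group |
|---|---|---|
| 34 | 0.936 | 0.888 |
| 30 | 0.924 | 0.841 |
| 27 | 0.913 | 0.796 |
| 23 | 0.891 | 0.721 |

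The pre/post comparison stays above 0.80 throughout. The three-measure analysis falls below 0.80 at an assumed 20% loss. The main issue is selection, which a larger sample would not cure.

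**4. Size of the selection effect (illustration only)**

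If a share d leaves, the mean among stayers exceeds the mean among all starters by d × (stayer mean − leaver mean).

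- *Effect.* If stayers gain Δ and leavers gain 0, the average gain among starters is (1 − d)Δ and the overstatement factor is 1/(1 − d): 1.11, 1.25 and 1.43 for d = 0.1, 0.2 and 0.3. If leavers gain half as much as stayers, the factor is 1/(1 − d/2): 1.05, 1.11 and 1.18.
- *Satisfaction (CSQ, 1 to 4).* If stayers average 3.5 and leavers would have averaged 2.5, the gap is 1 point and the reported mean is too high by 0.1, 0.2 or 0.3. If leavers would have averaged 2.0, the mean over all starters is 3.35, 3.20 or 3.05 against a reported 3.5.

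**The case against.** The strongest reply is that Table 1 is an outline of what attenders do, and that tracing absentees is operational detail which an article leaves to the fuller protocol. In part this stands. A reader might infer that leavers will never be asked, but the article does not say so; that reading comes from the schedule and from silence. The point does not rest on silence alone, however. The article itself fixes the collections in the last session and states the discard rule, and together these give results from completers only.

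A second reply is that controls are measured under equal conditions. Section 2.5.2 does say this, and waiting-list parents can also be lost, so it would be wrong to present unequal loss as established. But equal terms of collection do not remove the difference that only one arm has a programme to leave.

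A third reply is that a reader might infer that all evaluation happens inside sessions. It does not. The 6-month battery and Table A4 lie outside them, and Table A4 asks about changes noticed and about barriers to practice. Parents leaving after session 6 will have completed the feedback form. Barriers and transfer to daily life may therefore be partly covered. Neither source carries a satisfaction scale or replaces the post-test, and a leaver's 6-month battery without a post-test would still be an incomplete case in the three-measure analysis.

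Finally, a reader might take the phrase "carry out this content and thematic analysis using a representative sample" in section 2.6.2 as a claim that completers represent all who started. The sentence concerns saturation and the number of focus groups, and it covers the questionnaire content analysis as well as the themes. It does not support that reading.

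**Conclusion.** The concern holds in this form: as written, the pre/post comparison, the CSQ mean and the discussion-group themes would describe parents still attending at the end, not all who began. The likely direction is favourable to the programme, on the plausible but unverified premise that leavers did less well or were less satisfied; parents who leave for other reasons would weaken it.

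The size cannot be determined from the article. The factor of 1.11 to 1.43 requires 10% to 30% leaving and no benefit at all to leavers, and it shrinks as soon as leavers gain something. The CSQ figures rest on assumed means. No stated sample-size figure is wrong on this account. The change is worth making before data collection because a post-test that was not requested cannot be recovered later.

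**What to change.** In section 2.5.2 and Table 1, separate measurement from attendance:

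- State that every parent who completed the pre-test is offered the self-administered effectiveness battery and the CSQ at the planned session-11 date, and the 6-month battery and questionnaire, whether or not they are still attending. Absentees receive them by email or telephone.
- Add one or two open questions for leavers: the reason for leaving, and what did not help.
- In section 2.6.1, analyse all parents with a post-test whether or not they stayed, and report the numbers who started and who answered beside the CSQ and the qualitative results.
- In section 2.6.2, state that the discussion-group themes come from parents who attended the final session. Do not attach this wording to the whole saturation sentence, because the content analysis draws on other questionnaires.

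The cost is small. Email is already used for home-practice materials (section 2.5.1), two data collectors are in place (section 2.5.2), and Table A3 records attendance for each participant at each session, so absentees can be identified. If the consent form does not already separate leaving the programme from leaving the study, one line would do so. The drawbacks are that some leavers will not reply and that those who do will have completed the forms in a different way. Both should be reported.
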